### Sample size calculation

For the objective of developing the optimal risk prediction model for Chinese AF population, a minimum of 200 events (i.e. 10 times of the variable number) are required to accommodate 20 variables in the prediction model. The analysis is planned to be done in 2015 to accumulate enough events for analysis. For that purpose, about 5000 patients without anticoagulation therapy are required for an evenly splitted training cohort and validation cohort. For the objective of evaluating the effectiveness of ablation therapy, the following assumption is made: the accumulate ischemic stroke and intracranial hemorrhage is 10 % in optimally anticoagulated patients and 7 % in ablation patients in five years, 1800 matched patients in each arm are required to provide 90 % power to detect the difference (α = 0.05). As those two groups of patients are quite different, we amplified the sample size by 3 times to guarantee enough matched patients. In total, 16000 patients are required for the main analyses and considering a possible 20 % withdraw and loss of follow up, we up round the sample size to 20000.

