### Clinical data collection

Key data elements and definition of each variable were in line with the ACC/AHA recommendation on AF clinical data standards [9] and international peer studies [10] to facilitate cross-comparison of results between different registries. The following data were collected for each patient enrolled: basic socio-demographic information, symptoms and signs relating to AF, medical history, results of physical examination and laboratory test and patient self-reported quality of life (using a validated Chinese version of AFEQT questionnaire). For patients undergoing ablation therapy, detailed procedure related information is also collected, including the pathway of ablation, achievement of conduction block, time consumed and peri-procedure complications.

Each enrolled patient will be followed up every 6 months by trained staff, at outpatient clinic or through telephone interview. Information relating to medical therapies, health-care utilization, and clinical outcomes will be collected during follow up. Definition of the major outcome events are provided in Table 2. Every patient will be followed up until 2020. The questionnaires used for data collection in study are provided in appendix. All the data were entered into a specific electronic data capture system.

**Table 2 Tab2:** Outcomes collected and associated definitions

Outcomes	Definitions
Primary outcome	
Composite outcome of any of the following events: all-cause mortality, non-fatal ischemic stroke and peripheral embolism.	All-cause mortality: All deaths regardless of etiology
	Non-fatal Ischemic stroke: Documented stroke or cerebrovascular accident consisting of acute loss of neurological function caused by an ischemic event with residual symptoms at least 24 hours after onset.
	Peripheral embolism: Abrupt vascular insufficiency associated with clinical and radiological evidence of arterial occlusion in a vascular bed other than the cerebrovascular system in the absence of other likely mechanisms (e.g., atherosclerosis).
Secondary outcomes	
Component of the primary composite outcome including: 1) all-cause mortality; 2) non-fatal stroke or peripheral embolism.	As above
Intracranial hemorrhages	Bleeding into or around the brain, including 1) Hemorrhagic conversion of a primary ischemic stroke; 2) Subarachnoid hemorrhage; 3) Intra-cerebral hemorrhage; 4) Other (including subdural and epidural hematomas);

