Unadjusted event rates for the composite primary outcome of time to first all-cause mortality, stroke and peripheral embolism for the propensity-matched ablation and non-ablation groups will be estimated using the Kaplan-Meier method and compared between groups with the log-rank test. As sensitivity analyses, the inverse probability of treatment weighting using propensity score will also be used to compare the survival distributions between ablation and non-ablation group.

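### The 90% power for the ablation comparison is calculated for ischemic stroke plus intracranial hemorrhage, not for the primary composite that the comparison tests, so the power of that comparison is unstated

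*Protocol article*

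**What the plan says.** **Sample size calculation.** The assumption for the ablation objective is that "the accumulate ischemic stroke and intracranial hemorrhage is" "10 % in optimally anticoagulated patients" and "7 % in ablation patients in five years". From this the article concludes that "1800 matched patients in each arm are required" "to provide 90 % power to detect the difference (α = 0.05"). The figure is then multiplied by three to allow for patients who cannot be matched, and it feeds the totals of 16000 and 20000.

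**Table 2 (Clinical data collection).** The primary outcome is a composite of "all-cause mortality, non-fatal ischemic stroke and peripheral embolism". Intracranial hemorrhage is listed separately, as a secondary outcome.

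**Statistical analysis.** The matched ablation and non-ablation groups are compared by Kaplan-Meier and log-rank test on the "composite primary outcome of time to first all-cause mortality, stroke and peripheral embolism".

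**Research objectives, item (iii).** The comparison of ablation with medical therapy concerns death and thromboembolic events. This agrees with Table 2.

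**The concern.** The endpoint behind the 90% and the endpoint tested share only ischemic stroke. The powered endpoint contains intracranial hemorrhage, which the Table 2 composite does not. The composite contains death and peripheral embolism, which the powered endpoint does not. The article gives no five-year rate and no expected effect for death, for embolism or for the composite.

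This is the only power statement for the third main objective, and a reader would naturally take 90% to be the power of the primary comparison. Adding all-cause death changes both the number of events and the average treatment effect across them. More events raise power, while events that ablation does not influence dilute the effect and lower it. Which of the two dominates depends on assumptions the article does not state. Without them, neither the adequacy of 1800 pairs nor the precision behind a neutral result can be judged for the outcome that matters.

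**Working it through.** **1. Reproduce the stated figure.** Inputs from Sample size calculation: p1 = 0.10, p2 = 0.07, α = 0.05, power 90%, 1:1 matching. Sidedness is not stated, so two-sided is taken. With mean risk p̄ = 0.085:

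- √(2p̄(1−p̄)) = √0.15555 = 0.3944
- √(p1(1−p1) + p2(1−p2)) = √(0.0900 + 0.0651) = 0.3938
- n = (1.960 × 0.3944 + 1.2816 × 0.3938)² / 0.03² = 1814 per arm
- Power at n = 1800: z = (0.03 × √1800 − 1.960 × 0.3944) / 0.3938 = 1.269, which gives **89.8%**

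Unpooled variance gives 1811 per arm. Schoenfeld's log-rank formula (hazard ratio ln 0.93 / ln 0.90 = 0.689) gives 303 events, or about 1782 per arm. A one-sided test would need only 1479. So 1800 is right for 10% v 7%, two-sided.

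**2. Compare the endpoints.**

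| Component | Powered endpoint | Primary outcome, Table 2 |
|---|---|---|
| Ischemic stroke | yes | yes (non-fatal) |
| Intracranial hemorrhage | yes | no (separate secondary) |
| Death from any cause | no | yes |
| Peripheral embolism | no | yes |

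**3. Power for the composite at 1800 per arm.** The article supplies no inputs, so all of the following are assumptions:

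- 2 of the 10 points are hemorrhage, leaving 8% ischemic stroke in controls. The same proportional reduction (7/10) gives 5.6% after ablation.
- Five-year control mortality is 5%, 10% or 20%.
- Stroke and death are independent, so composite risk = 1 − (1 − stroke)(1 − death).
- Peripheral embolism adds nothing.

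The power formula is the one in step 1. Example, 10% mortality and no effect on death: control 1 − 0.92 × 0.90 = 17.2%, ablation 1 − 0.944 × 0.90 = 15.04%, power 42%.

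| Control mortality | Death unchanged | Death cut by 10% | Death cut by 20% |
|---|---|---|---|
| 5% | 57% (12.6 v 10.3%) | 74% (12.6 v 9.8%) | 87% (12.6 v 9.4%) |
| 10% | 42% (17.2 v 15.0%) | 73% (17.2 v 14.1%) | 92% (17.2 v 13.2%) |
| 20% | 26% (26.4 v 24.5%) | 76% (26.4 v 22.6%) | 98% (26.4 v 20.7%) |

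**4. Sensitivity to the hemorrhage share.** If the full 10% v 7% is carried into the composite and death is unchanged, power is 72%, 57% and 37% at 5%, 10% and 20% mortality. The low values in the first column do not depend on the 2-point split.

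**5. Effect carried over whole.** If hazard ratio 0.689 applied to the entire composite, death included, at assumed control rates of 15% to 30%, power would run from 97.8% to over 99.9%. If only the 3-point absolute difference carried over, it would be 75.0% at a 15% control rate, falling to 51.3% at 30%.

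**The case against.** Several points on the other side have force.

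- **Nothing is miscalculated.** Correct: step 1 reproduces the figure. This is an internal inconsistency between sections, not an arithmetic error.
- **Underpowering is not shown.** A reader might infer from the mismatch that the ablation comparison is underpowered, or that correct figures would probably look worse. The documents do not support either. They give no mortality rate and no effect on death, and objective (iii) contemplates a reduction in death. With a 20% cut in death, power passes 90% at 10% mortality and above.
- **There is no third endpoint.** A reader might take the unqualified word for stroke in Statistical analysis to include hemorrhagic stroke. But that sentence names the primary outcome, which Table 2 defines as ischemic. Table 2 uses the same shorthand in its own secondary row, and Data management and quality control sends ischemic stroke and peripheral embolism to adjudication.
- **1800 is a minimum.** The threefold allowance may yield more pairs. At 3000 pairs, the case of 10% mortality with a 10% cut in death rises from 73% to 91%. That is true, but the 90% is attached to 1800.
- **A fuller plan may analyse stroke plus hemorrhage.** Possible, and both components are collected. The statement that no analysis uses that composite is therefore limited to this article. A further analysis elsewhere would still not transfer the 90% to the primary comparison.
- **A non-significant log-rank test is not proof of no benefit at any power.** Agreed, and the article also plans Kaplan-Meier event rates by group.

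These narrow the point but leave the mismatch itself standing.

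**Conclusion.** The concern holds as an endpoint mismatch. The 90% at 1800 matched patients per arm belongs to a composite that the article neither lists as an outcome nor analyses, and no power is given for the primary comparison of ablation with non-ablation. Under the assumptions in step 3, that power is anywhere from 26% to 98%. The effect on death decides most of it: 57% down to 26% with none, 87% to 98% with a 20% reduction. If hazard ratio 0.689 held throughout, it would be about 98% to over 99%. These are illustrations of how much is left open, not estimates.

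The point should be corrected because the plan relies on the figure for a main objective. It is not critical: it alters no outcome definition, analysis method or enrollment target.

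**What to change.** In Sample size calculation, do one of the following:

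1. Restate the power for the Table 2 composite at 1800 matched pairs. Give the assumed five-year control rates of death, ischemic stroke and embolism and the assumed effect on each, with a range that includes both no effect on death and a reduction in death.
2. Keep the 90%, name ischemic stroke or intracranial hemorrhage as a secondary composite in Table 2, assign it an analysis in the matched groups, and say that the 90% refers to that outcome. The article should then state that power for the primary composite was not the basis of the sample size.

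Optionally, write non-fatal ischemic stroke in Statistical analysis so that the wording matches Table 2.

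The cost is a few sentences and a short recalculation. No added patients are needed; 17467 were already enrolled by June 30, 2015. The restated power may come out higher or lower than 90%.

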## Results

### Current status and data quality

17467 patients had been enrolled as at June 30, 2015. The majority (84.0 %) came from tertiary hospitals where most AF patients are managed. The missing rates for the key variables are listed in Table 3. There are no missing data among the mandatory variables which is controlled by the EDC system. Out of range variables were very rare (<0.1 %) for those with range check. Patient follow up rates at 6, 12, 18 and 24 months are 93, 91, 87 and 85 % respectively.

**Table 3 Tab3:** Variables collected in the CAFR study and missing rate for each key variables

Variables	Number of variables currently collected	Missing rate (%)
Age or Date of Birth	17467	0 %
Sex	17467	0 %
Date of initial register	17467	0 %
Type of AF	17340	0.73 %
Systolic blood pressure	17291	1.01 %
Height	15845	9.29 %
Body weight	15964	8.60 %
History of alcohol-drinking	17250	1.24 %
History of hypertension	17331	0.78 %
History of diabetes mellitus	17331	0.78 %
History of hyperlipidemia	17288	1.02 %
History of heart failure	17331	0.78 %
History of myocardial infarction	17328	0.80 %
History of coronary artery disease	17330	0.78 %
Signs of heart failure	17329	0.79 %
Hemoglobin level	13552	22.4 %
Creatinine level	14264	18.3 %
Fasting blood glucose	13718	21.4 %
Total cholesterol	13587	22.2 %
Is thyroid function within normal range	12367	29.2 %
Left ventricular ejection fraction	13568	22.3 %
History of direct current cardioversion	17268	1.14 %
History of radiofrequency ablation	17332	0.77 %
History of ischemic stroke/transient ischemia attach/ peripheral arterial thromboembolism	17338	0.74 %
History of intracranial hemorrhage/other major bleeding	17335	0.76 %
Use antiarrhythmic agents	17334	0.76 %
Use ventricular rate control agents	17332	0.77 %
use antithrombotic agents	17333	0.77 %
Warfarin	17281	1.06 %
Use Angiotensin converting enzyme inhibitors/angiotensin receptor blockers	17281	1.06 %
Use Statins	17283	1.05 %

## Discussion

This large, contemporary, longititudinal study of Chinese AF patients will provide a unique opportunity to answer many clinical questions and to expand our knowledge of AF development and treatment.

**Table 4 Tab4:** Atrial fibrillation registry studies worldwide

Studies	Participating centers	Timeline	Follow-up	Sample size	Main purpose
RHYTHM-AF [18]	10 countries, 175 centers, mostly European countries	May 2010 ~June 2011	60 days	3940	To describe treatment patterns and short term outcomes related to cardioversion.
GARFIELD [19]	50 countries in Europe, Asia-Pacific, Central/South America, and Canada	Started in December 2009, with a planned recruitment period of 4 years	2-year	55,000	To evaluate the management and outcomes of patients with newly diagnosed non-valvular AF at risk for stroke.
GLORIA-AF [20]	Nearly 50 countries in Asia, Europe, North America, Latin America and Africa/Middle East	Phase I: May 2011- January 2013.	Phase II: 2 years	56,000	To investigate patient characteristics influencing choice of antithrombotic treatment and to collect data on outcomes of antithrombotic therapy
		Phase II: November 2011	Phase III: 3 years		
		Phase III: early 2014			
J-RHYTHM [21]	158 institutions in Japan	January to July 2009	2-year	7937	To determine the appropriate INR for Japanese AF patients
PINNACLE-AF [22]	In the United states	October 2011	-	>300000	Quality improvement
The Atrial Fibrillation Ablation Pilot Study [23]	72 centers in 10 European countries	October 2010	1 year	1410	to describe the clinical epidemiology and treatment of patients undergoing AF ablation
ORBIT-AF [24]	200 US outpatient practices	June 2010 to August 2011.	≥2 years	10097	To characterize treatment and outcomes of patients with AF

*Abbreviations*: *RHYTHM-AF* International Registry on Cardioversion of Atrial Fibrillation, *GARFIELD* Global Anticoagulant Registry in the FIELD, *GLORIA-AF* Global Registry on Long-Term Oral Antithrombotic Treatment in Patients with Atrial Fibrillation, *J-RHYTHM* Japanese Rhythm Registry, *PINNACLE-AF* The nationwide US Practice INNovation And Clinical Excellence Registry, *ORBIT-AF* The Outcomes Registry for Better Informed Treatment of Atrial Fibrillation

The CAFR study is important in several respects. First, systematic observational data can be generated from this registry study, which is especially valuable given that evidence for Chinese AF patients is limited. Results from randomised clinical trials remain the most robust evidence for clinical decision making, these can be expensive and time consuming to be feasible in many scenerios. Second, treatment of AF is changing dramatically. For example, ablation therapy is increasingly widely provided while there is short of evidence to support the practice, especially in the Chinese AF population. NOACs have proved their efficacy in stroke prevention [13–17] but whether the efficacy observed in randomized trials translates into effectiveness and safety in Chinese AF patients need to be evaluated in real world studies. Third, the CAFR study provides a good opportunity to compare treatment and response variation among AF populations in China, for comparison with different countries. Currently, several other large AF registries are ongoing. The main characteristics of large size registry studies are listed in Table 4.

The CAFR study is unique compared with other AF registry studies in the following respects: (i) CAFR is the largest real world study among Asian AF patients and will generate invaluable data for this patient group; (ii) CAFR is a longitudinal study which enable evaluation of long term effects of specific therapies; and (iii) A high proportion of patients had their blood sample taken, which enables investigation of genetic and environment interactions in the developement and treatment of AF.

### Limitations

Participating hospitals of this study are all hospitals in urban and semi-urban area of Beijing, the capital of China. However, about half of the registied patients come from all around the country, which increases the representativeness of the study population. In addition, the majority of patients are registred from tertiary hospitals, but this reflects current practice of Chinese medical care as the mechanisms of referral are not fully established and patients usually go direct to terriary hospitals without referral from primary health care providers. Despite these limitations, we feel that we are unlikely to overtly bias conclusions for the prespecified main analysis of this study.

## Conclusion

CAFR will be one of the largest registries of Asian AF patients (and the largest in Chinese AF patients), as well as providing the longest follow up. This study would provide a valuable opportunity for ‘real world’ clinical epidemiology with insights into the uptake (and outcomes) of contemporary AF management.

## Abbreviations

AF, atrial fibrillation; CAFR, Chinese atrial fibrillation registry; EDC, electronic data capture; INR, international normalized ratio; NOAC, non-vitamin K antagonist oral anticoagulants; OAC, oral anticoagulation; TTR, time in therapeutic range
